### Recruitment

A total of 50 participants will be recruited. We will address potential participants (whatever contact is preferable) from the already existing databases at CEITEC with people willing to be contacted and willing to participate in the neuroimaging projects. We will also utilize participants invited by doctoral students involved in the project. These will identify further potential participants (snowball). Flyers and posters will be disseminated on the university campus and surrounding public places.

### Assignment of Interventions: Allocation

#### Sequence Generation, Concealment Mechanism, and Implementation

All participants will be randomly assigned to the constant and variable practice condition groups (CG and VG, respectively) with a 1:1 allocation ratio. An online randomization generator^1^ with three blocks of four, three blocks of six, and two blocks of 10 participants will be used.

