### Sample Size

In order to calculate the sample size, we used mean and standard deviation (SD) values (Dean et al., 2013) presented by Cheng and colleagues in Table 1, specifically, values for Time Window 1 (T1) for novice and expert participants (Cheng et al., 2015). We set confidence interval = 95%; power = 0.8; ratio of sample size = 1 (constant practice group vs. variable practice group). As a result, a minimal sample size estimated was eight participants in total, four participants per group. Given, we were going to recruit novices for both groups, the possible drop-out, statistical requirements (e.g., at least five observations perc variable in regression models), and considering potential recording problems, we decided to measure 25 participants per group.

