### Assignment of Interventions: Blinding

#### Who Will Be Blinded

Given the nature of the intervention and the objectives of the study (basic science), neither participants nor the researchers will be blinded.

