### Who Will Take Informed Consent?

A team member, e.g., doctoral student, post-doc, or active researcher, will meet with prospective participants and explain the study’s objectives and all procedures and collect informed consent. If there was a dependent relationship between the team member and the potential participant (e.g., student—academic, patient—medical doctor), an independent person from Masaryk University would be asked to provide a short meeting to the potential participant(s). This independent person will be an active researcher with at least a doctoral degree. All of the issues of the dependent relationship will be discussed. Participants will be informed that they may resign at any time without any consequences.

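### The exact block make-up for all 50 places is published in an unblinded trial whose own staff recruit, with no stated separation from the allocation list: about 5% to 24% of assignments are certain in advance, and about 68% can be guessed

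*Protocol article*

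**What the plan says.** All places are in the Protocol article.

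- **Assignment of Interventions: Allocation.** Participants are randomised "with a 1:1 allocation ratio". The method is "An online randomization generator" "with three blocks of four, three blocks of six, and two blocks of 10 participants will be used". The heading covers sequence generation, concealment and implementation, but the text gives only the ratio, the generator and the blocks. Block order is not given, nor is who generates, holds or releases the list.
- **Sample Size and Recruitment.** "we decided to measure 25 participants per group", and "A total of 50 participants will be recruited".
- **Blinding.** "neither participants nor the researchers will be blinded".
- **Recruitment.** Besides an existing database, snowballing, flyers and posters: "We will also utilize participants invited by doctoral students involved in the project".
- **Who Will Take Informed Consent?** "A team member, e.g., doctoral student, post-doc, or active researcher, will meet with prospective participants" and collect consent.
- **Table 1.** Eligibility screening and consent stand in the enrolment column, ahead of a separate allocation column.

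**The concern.** Blocks of mixed size are used so that staff who see past assignments cannot tell where a block ends. Publishing how many blocks of each size exist, when together they fill the whole trial, gives part of that protection away. Here past assignments are visible to unblinded researchers, and the people who invite and consent come from the same project. Research assistants schedule all visits (Plans to Promote Participant Retention), so order of entry could in principle be influenced.

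At stake is selection bias: someone expecting a given arm next could bring a particular volunteer forward or hold one back. Two features make this harder to repair afterwards.

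- Anyone who misses a training session or a test is removed from the analysis, so a difference between arms in likely attendance would change who is analysed.
- In the step-contraction test the variable group performs three patterns and the constant group one, at pretest as well. For that outcome a baseline comparison between arms is not like for like. The MRI and the 20% MVC potential paradigm are common to both arms and do not have this limitation.

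**Working it through.** **Inputs** (Allocation, Sample Size and Recruitment sections): three blocks of 4, three of 6, two of 10; 1:1 within blocks; 50 participants, 25 per group.

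**Step 1. Reproduce the total.** 3×4 + 3×6 + 2×10 = 12 + 18 + 20 = 50. Half of each block gives 25 per arm. The published blocks match the recruitment target exactly.

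**Step 2. Block order known (for example, run as listed).** Take a block of 2m places, m per arm, with past assignments visible.

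- A place is certain once one arm is used up. Expected certain places per block = 2m/(m+1).
- The best guess is the arm with more places left, with a coin toss at a tie. Expected correct guesses per block = m + 2^(2m−1)/C(2m,m) − 1/2.

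| Block size | Number | Certain per block | Correct guesses per block |
|---|---|---|---|
| 4 (m=2) | 3 | 4/3 = 1.33 | 2 + 8/6 − 0.5 = 2.83 |
| 6 (m=3) | 3 | 6/4 = 1.50 | 3 + 32/20 − 0.5 = 4.10 |
| 10 (m=5) | 2 | 10/6 = 1.67 | 5 + 512/252 − 0.5 = 6.53 |

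- Certain: 3×1.333 + 3×1.50 + 2×1.667 = 4.00 + 4.50 + 3.33 = 11.83 of 50, or 23.7%.
- Correct guesses: 3×2.833 + 3×4.10 + 2×6.532 = 8.50 + 12.30 + 13.06 = 33.86 of 50, or 67.7%.

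An exact recursion over the permuted blocks gives the same values.

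**Step 3. Block list known, order random and unknown.** All orders were taken as equally likely, and the probability of each arm was updated after every assignment (3,000 simulated trials). On average 2.4 of 50 places (4.9%) are certain, and 33.9 of 50 guesses (67.8%) are correct. The last place is always certain, because 25 per arm leaves only one possibility once 49 are seen.

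**Step 4. Block sizes not known at all.** Every completed block is balanced, so the running difference between arms always equals the difference inside the current block. Guessing the arm that is behind overall is therefore the same rule as in Step 2. Simulation (20,000 trials) gives 67.7%.

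**Reading.** Knowing the block list adds certainty about some places, mostly at block ends. It does not change the average guess rate, which is about 68% in Steps 2, 3 and 4.

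**The case against.** - **A journal article condenses.** Who holds the list and how it is released may sit in the full protocol. This stands, and their absence is not the point here. What the article does fix is the full block composition, and no later document can withdraw that.
- **Publication does not cause the guess rate.** This stands. A reader might infer that the 68% comes from publishing the blocks, or that shuffling them would lower it. Step 4 shows otherwise: it comes from small balanced blocks with visible history. Only the certainty figure depends on the block list and its order.
- **The 24% rests on an assumed order.** This stands. The article states no order, so 24% is the upper case and about 5% the lower.
- **The team is not said to allocate or hold the list.** This stands. A reader might infer complete predictability from an open list in the recruiters' hands, or that doctoral students invite acquaintances. The article says neither. Nor does it say that every inviter sees the running allocation.
- **Consent already precedes allocation.** This stands for Table 1. It does not stop someone from timing an invitation or booking on an expected next arm.
- **There is little motive and no measured harm.** The article calls the choice of comparator arbitrary and gives both arms the same number of trials and training time. Pre-practice measurement would also show some imbalances. This lowers the likely harm without removing the opportunity.

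**Conclusion.** The point holds in a limited form. The article discloses a block set that fills the trial exactly, researchers are unblinded, project staff invite and consent, and no separation from the list is stated. For someone who sees past assignments, between about 5% (order unknown) and 24% (order as listed) of places are certain in advance, always including the last. About 68% can be guessed whether or not the sizes are known.

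These figures assume that the observer sees every past assignment, that the 50 places are filled in sequence, and that excluded participants are not replaced. They measure predictability, not bias in any outcome. A reader might conclude that enrolment will be steered; the article shows only that it could be. The change is cheap and worth making.

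**What to change.** 1. Replace the published list with a new one whose block sizes and order are not disclosed to the team. This removes most of the block-end certainty. If the new list again ends at exactly 25 per arm, the last place stays deducible from a full tally; a list longer than 50 would avoid that.
2. Release each assignment singly, through a web-based system or someone not involved in recruitment or testing, and only after eligibility and consent are irrevocably recorded. Table 1 already has this order. What is added is the locked record and the independent release, so that a correct guess cannot undo an enrolment.
3. Where feasible, keep the running tally from those who invite and book participants. This is the step that acts on the 68%. In an unblinded trial with a small team it may be only partly achievable.
4. State in the Allocation section who generates, holds and releases the sequence.

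The cost is generating a list and a short wait for each assignment. No participants, visits or measurements are added. If some participants have already been allocated, the new list would cover the remaining places only.

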### Assignment of Interventions: Blinding

#### Who Will Be Blinded

Given the nature of the intervention and the objectives of the study (basic science), neither participants nor the researchers will be blinded.

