The participants from VG will perform three types of SPSICs (1–3), each repeated 15 times (together 45 trials), but the participants from CG will perform 45 times of one type of SPSIC. This SPSICs will be analyzed in the frequency domain using force signal as a trigger for extracting SPSIC sequences related to time frames of EEG time series data. We will estimate EEG signal’s power spectrum density (PSD) for sensorimotor rhythm (SMR, frequency band 12–15 Hz) as well as for other frequency bands: delta (0.5–4 Hz), theta (4–8 Hz), alpha (8–14 Hz), beta (14–35 Hz) and gamma (35–70 Hz). PSD-EEG analysis will reveal the level of the electrical activity of cortical regions engaged during UIFA motor tasks performance under the constant and variable practice conditions. We will also estimate coherence between EEG signals (EEG-EEG coherence) from electrodes in a chosen region of interest based on the PSD-EEG analysis. Analysis of EEG-EEG coherence calculates the linear relationship between the power spectra of two EEG signals taken from two EEG electrodes placed on the scalp. A significant linear relationship existing between time series simultaneously recorded from two locations (high coherence) indicates a high level of functional communication (connectivity) between these areas of the cerebral cortex, whereas low coherence indicates the opposite.

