### Confidentiality

All data will be coded, and data processing will be performed on coded entries. The only file allowing to identify a participant personally will be kept in the PI’s computer. The identifying file will be kept for 5 years and will be anonymized afterward. The data from the MRI safety form and original MRI recordings containing personal data will be secured and processed by the authorized employee of the MAFIL facility. Pseudonymized (coded) data will be used for subsequent data processing.

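### The reasons given for blinding no researcher do not reach MRI processing or MRCP-EEG processing, where the data do not show the group

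*Protocol article*

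**What the plan says.** The section Who Will Be Blinded consists of one sentence. It gives two reasons, the nature of the intervention and the basic-science aim, and concludes that "neither participants nor the researchers will be blinded". It makes no exception for people who process or model the recordings.

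The Confidentiality section describes the data flow: "All data will be coded, and data processing will be performed on coded entries". For the MRI data it adds: "Pseudonymized (coded) data will be used for subsequent data processing". On the key it says: "The only file allowing to identify a participant personally will be kept", namely on the principal investigator's computer. The section concerns personal identity. It does not say that the codes hide the allocated group.

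The Outcomes section fixes what each group does when measured:

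- **MRI.** Structural, diffusion and resting-state scans. No practice pattern is performed in the scanner.
- **MRCP EEG.** Forty identical trials for both groups.
- **SPSIC EEG and force.** The variable group performs three patterns, 15 times each, "but the participants from CG will perform 45 times of one type of SPSIC". The EEG segments are cut "using force signal as a trigger for extracting SPSIC sequences related to time frames of EEG time series data".

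**The concern.** A decision not to blind should go only as far as its reason. Here the nature of the intervention prevents masking of some people, but the sentence applies it to everyone. The second reason, a basic-science aim, is no obstacle to withholding a group label from someone processing a scan.

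The imaging and EEG results pass through processing choices before any group comparison. If those choices are made with the group known, they can drift towards the result that the team expects, and the later analysis can neither detect nor undo this. The Background and Rationale does state some directional expectations, for example higher SMR under variable practice and lower sensorimotor and prefrontal activation under constant practice. The article also says that there is no monitoring committee and no independent audit, so nothing else in the plan acts as a check.

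**Working it through.** The document gives no figure on this point and none can be derived, so the check sets the blinding sentence against what each data stream contains.

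1. **Training sessions.** The constant group practises one pattern and the variable group three. Participants and trainers see this, so the stated reason holds for them.

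2. **SPSIC test: EEG and force.** Variable group: 3 patterns × 15 = 45 trials. Constant group: 1 pattern × 45 = 45 trials. The totals match, but the force trace shows whether one pattern or three were performed, and that trace also triggers the EEG segments. Test staff and anyone handling these files can read the group from the content. The stated reason holds here too.

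3. **MRCP EEG.** 40 trials in each group, with the same target force and the same timing. The task does not show the group, so the stated reason does not hold.

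4. **MRI.** Structural, diffusion and resting-state acquisition involves no group-specific task. The images do not carry a group label, so the stated reason does not hold.

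5. **Are there choices in streams 3 and 4 that group knowledge could influence?** Yes, from the article's own description. MRCP: dipole source analysis and connectivity analysis. MRI: definition of specific tracts by tractography, independent components, and cortical thickness, which is worded as optional. The discretion has limits: Plans for Assessment and Collection of Outcomes names the resting-state regions and the four networks of emphasis in advance. The Sample Size section anticipates recording problems, so some decisions on data quality are likely, although the article describes no rejection rule.

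6. **Choices in the SPSIC stream.** The electrodes for EEG-EEG coherence are chosen after the power-spectrum results are seen. The Outcomes section places this in the SPSIC analysis, where the group is visible. Masking the MRI and MRCP processors would not reach that choice; it has to be handled by fixing the rule before groups are compared.

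7. **Does the existing coding already solve the problem?** No. Pseudonyms conceal who a participant is. A processor who holds the allocation list, or who can link a participant's MRCP or MRI file to that participant's SPSIC file through a shared code, still knows the group.

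**The case against.** The strongest reply is that the open design is disclosed and given a reason, in a mechanistic study of healthy volunteers, and that the SPSIC test reveals the group to far more people than the trainers. Much of this stands. A reader might infer that the intervention prevents blinding only of participants and trainers. The Outcomes section does not support that, since SPSIC testers and everyone handling SPSIC force or EEG files can also see the group.

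A reader might also infer that blinding would cost nothing because the files are coded already. The Confidentiality section describes coding of identity, so a further step is needed. Nor can the SPSIC stream be masked by passing on only the pattern common to both groups. Taking the constant group's test pattern to be SPSIC 1, the only one it trains on, the counts would be 15 against 45 and would identify the arm. It would also discard 30 of the variable group's 45 trials.

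Further limits apply. The expectations are not directional throughout: for coherence, the Background and Rationale expects no difference between groups given equal practice. The article nowhere says that small effects are expected; its Sample Size calculation arrived at four per group, which implies a large one.

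What the reply does not answer is why the scans and the MRCP recordings need to be processed with the group known. The point cannot be left to a separate analysis plan either: the article does not merely omit blinding of processors, it states that no researcher is blinded, and a later plan that masked them would contradict it.

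**Conclusion.** The concern holds for MRI processing and MRCP-EEG processing. For these, neither stated reason justifies leaving the processors unblinded, the data do not reveal the group, and there are choices that group knowledge could influence. It does not hold for participants, trainers, SPSIC test staff, or handlers of SPSIC EEG and force data.

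The size of any bias is not estimable from the document. A figure would require an assumed shift in an outcome, and no section supplies one. The conclusion rests on two readings: that the word researchers includes those who process the data, since no exception is made, and that scanning involves no group-specific task, as the Outcomes section describes. This is an avoidable weakness in the design that should be corrected; it is not a contradiction that invalidates the plan.

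**What to change.** Replace the sentence under Who Will Be Blinded with text to this effect:

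> Participants, trainers and SPSIC test staff are not blinded. MRI and MRCP-EEG processing, quality exclusions and region, component and tract choices are made on coded files without group allocation, by processors who do not have the allocation list, and are locked before allocation is merged. SPSIC EEG and force data are processed with group visible, and their processing rules are fixed before group comparison.

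Add to the Confidentiality section that the allocation list is stored apart from the coded files. The codes on the MRI and MRCP files should not let their processors link them to the SPSIC files, because those would disclose the group. The SPSIC rules to be fixed in advance should include how the coherence electrodes are chosen from the power-spectrum results.

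The cost is a re-coding or separation step and a lock date that must pass before group comparisons start. No new data are required.

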### Data Collection and Management

#### Plans for Assessment and Collection of Outcomes

Pretest, posttest, and retention tests will consist of MRI, EEG, and motor task proficiency assessments.

Changes in the gray matter will be estimated using voxel-based morphometry (Ashburner and Friston, 2000), which constitutes the whole-brain gray matter probabilities comparison. In addition, volumetric analyses will be calculated on both cortical and subcortical structures, and cortical thickness can be evaluated (Fischl et al., 2002). Variations in white matter microstructure can be assessed using Tract-Based Spatial Statistics (TBSS; Smith et al., 2006)—a method that applies voxel-wise statistics on diffusion metrics using projection onto an alignment-invariant tract representation. Representations of specific tracts can be obtained with probabilistic tractography (Behrens et al., 2007) that takes into account crossing fibers in individual voxels. The BOLD multi-echo echo-planar imaging (ME EPI) fMRI sequence will be applied regarding resting-state fMRI data. Representative time-series within chosen regions of interest (ROIs), i.e., dorsolateral prefrontal cortex, posterior parietal cortex, posterior parietal cortex, primary motor cortex, anterior cingulate cortex, cerebellar cortex, cerebellar dentate, putamen, thalamus primary, and motor cortex, will be extracted and used for seed-based analysis computation. Moreover, Independent Component Analysis (ICA) will be calculated in order to evaluate changes in large-scale brain networks’ connectivity, with the emphasis on fronto-parietal control network, dorsal attentional network, basal ganglia network, and sensorimotor network.

In order to test the sensorimotor cortex activity in constant and variable practice conditions, we decided to record the sensorimotor rhythm (SMR), which oscillates between 12 and 15 Hz in the motor cortex. SMR is widely used to indicate the activity of the sensorimotor cortex (Egner and Gruzelier, 2001, 2003) since there is a positive relationship between SMR power and inhibition of sensorimotor cortex activity.

Motor task proficiency will be measured as efficiency in repeating patterns of step isometric contractions (SPSIC) during UIFA using custom-made equipment.

### Plans to Promote Participant Retention and Complete Follow-Up

All assessments and training sessions will be scheduled by research assistants who will contact them prior to their visit.

### Data Management

Original EEG, demographic and personal data will be stored in a secure, MU password-protected repository. The original non-anonymized file will be password protected (two-phase authentication).

MRI safety forms are archived at a secured place at the MAFIL core facility. Electronic data from these forms is stored in a secured database (with two-phase authentication) by ICS MU. Original MRI data are stored in secure MEDIMED infrastructure (suitable for dealing with medical/healthcare data) provided by ICS MU.

